#### Motion Analysis

A 3D biomechanical motion analysis for kinetics and kinematics parameters will be recorded with the Vicon-Nexus 3D motion capture system (Vicon Vero, v2.2). Reflective markers (clusters) will be placed on the midpoint between the left shoulder and left elbow, the midpoint between right shoulder and right elbow, the midpoint between the left elbow and left wrist, the midpoint between the right elbow and right wrist, and seventh cervical vertebra and sacral region (midpoint between right posterior superior iliac and left posterior superior iliac) [25]. Additional markers will be placed on the screwdriver (top of the shaft) by the same experienced examiner. 3D marker trajectory data will be collected at 100 Hz with 6 cameras. Before starting the calibration, all reflective objects will be removed from the workspace so that they do not interfere with the recording. Necessary care will be taken to warrant that the worker’s clothing is also nonreflective [26]. Prior to the assessment of the subjects, the workstation will be prepared following the recommended procedures of calibration of both optical and video reference cameras according to the manufacturer's recommendations manual. The kinematic variables of interest are the range of motion of the neck, trunk, shoulder and elbow, speed, acceleration, and deceleration. The range of motion will be calculated as the maximum minus minimum joint angle in each selected sample.

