**Objective:**

This study protocol aims to explore the efficacy of a set of smart devices to detect malposture and increase postural awareness, reducing fatigue, and musculoskeletal disorders.

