### Data Collection and Outcomes

The primary outcomes are fatigue and musculoskeletal symptoms. Fatigue will be assessed by electromyography (EMG) and musculoskeletal symptoms by the Nordic Musculoskeletal Questionnaire [21].

Secondary outcomes include perceived effort, assessed by the Borg Rating of Perceived Exertion (RPE), range of motion of the main joints in the upper body and trunk, speed, acceleration, and deceleration of movement, through motion analysis, risk stratification of range of motion of the upper limb and trunk based on limits defined in the Rapid Upper Limb Assessment (RULA) [22], and cycle duration in minutes.

For patient characterization, baseline questionnaires including sociodemographic data, physical activity level, quality of life, anxiety and depression, insomnia and sleep quality, fatigue, and pain and disability will be collected. Table 1 displays the assessment flow.

**Table 1 table1:** Assessment flow.

Measurements	Initial measurement	At the start of the shift	During the shift	After the end of the shift
Sociodemographic information and habits	✓			
Quality of life—EUROHIS-QOL-8	✓			
Musculoskeletal pain (NMQ^a^) and adapted NMQ	✓	✓		✓
Physical activity (RAPA^b^)	✓			
Anxiety (GAD-7^c^) and depression (PHQ-9^d^)	✓			
Subjective fatigue (FACIT-F^e^)	✓			
Sleep quality (BaSIQS^f^)	✓			
Heart rate			✓	
Joint range of motion			✓	
Ergonomic risk (RULA^g^)			✓	
Electromyography			✓	
Perceived exertion (RPE^h^)		✓	✓	✓

^a^NMQ: Nordic Musculoskeletal Questionnaire.

^b^RAPA: Rapid Assessment of Physical Activity questionnaire.

^c^GAD-7: General Anxiety Disorder 7-item scale

^d^PHQ-9: Patient Health Questionnaire-9.

^e^FACIT-F: Functional Assessment of Chronic Illness Therapy—Fatigue.

^f^BaSIQS: Basic scale on insomnia complaints and quality of sleep questionnaire.

^g^RULA: rapid upper limb assessment.

^h^RPE: rate of perceived exertion.

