#### Ergonomic Risk

The RULA was selected to assess ergonomic risk in this study. This tool was developed to assess workers’ exposure to ergonomic risk work associated with musculoskeletal injuries of the upper limbs, taking into consideration biomechanical and postural load requirements of work task demands on the neck, trunk, and upper limbs. This instrument provides a simple scoring method based on the range of motion, which can identify joints at risk. The output of the RULA assessment tool is the final RULA score, which is a single score that represents the level of MSD risk for the job task being evaluated, ranging from a minimum of 1 to a maximum of 7 points [22].

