## Abbreviations

EMG: electromyography
GAD-7: General Anxiety Disorder 7-item scale
MSD: musculoskeletal disorder
PHQ-9: Patient Health Questionnaire-9
RAPA: Rapid Assessment of Physical Activity questionnaire
RPE: rating of perceived exertion
RULA: risk stratification of range of motion
WMSD: work-related musculoskeletal disorder

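### Read literally, the RULA risk strata are built on an excursion (maximum minus minimum angle), which cannot register a shift in working posture

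*Protocol article*

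**What the plan says.** The Data Collection and Outcomes section of the protocol article names, among the secondary outcomes, "risk stratification of range of motion of the upper limb and trunk based on limits defined in the Rapid Upper Limb Assessment (RULA". The Motion Analysis section defines the quantity: "The range of motion will be calculated as the maximum minus minimum joint angle in each selected sample". It also lists what will be taken from the recordings: "The kinematic variables of interest are the range of motion of the neck, trunk, shoulder and elbow, speed, acceleration, and deceleration". No mean, median or peak angle appears there, and no time spent in a posture.

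The Ergonomic Risk section describes RULA in two ways. It says "This instrument provides a simple scoring method based on the range of motion, which can identify joints at risk", and it also says that the tool works by "taking into consideration biomechanical and postural load requirements of work task demands on the neck, trunk, and upper limbs". It adds that "The output of the RULA assessment tool is the final RULA score", which runs from 1 to 7. The Abbreviations list expands the acronym as "RULA: risk stratification of range of motion". Table 1 puts joint range of motion and ergonomic risk (RULA) on separate rows.

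The stated objective is to "explore the efficacy of a set of smart devices to detect malposture and increase postural awareness".

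**The concern.** Posture is where a joint is held. Maximum minus minimum measures how far it travels. The two can move independently, so limits meant to grade postural load may not grade it when applied to an excursion.

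This matters because the feedback system is meant to make workers notice and correct awkward postures. One effect to expect is a change in working angle, and the RULA strata are the listed outcome closest to showing it. If they rest on an excursion, a worker who stays flexed but still could be graded low risk. A worker who straightens up without changing the amplitude of movement could show no change. One who leaves a fixed bad posture and moves more freely could appear to get worse.

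The Data Analysis section reads each worker's plot visually across the A and B periods. Such a correction would then appear as a flat line, or as a change in the wrong direction.

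**Working it through.** The article gives no figure to reproduce on this point. The check is an identity, with illustrative angles. All angles below are assumptions, because the article states neither joint angles nor RULA limits.

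**Inputs from the article**
- Range of motion (ROM) = maximum minus minimum angle within a sample (Motion Analysis).
- The quantity stratified is range of motion of the upper limb and trunk (Data Collection and Outcomes).
- Kinematic variables kept: range of motion, speed, acceleration and deceleration (Motion Analysis).

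**Step 1: the identity.** Add a constant c to every angle in a sample:

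(max + c) − (min + c) = max − min.

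ROM is unchanged for any c. Angular speed and acceleration are also unchanged, because a constant has zero derivative.

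**Step 2: same excursion, different postures.** A 10-degree movement at four assumed offsets:

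| Offset (degrees) | Range worked | ROM | Mean angle | Peak angle |
|---|---|---|---|---|
| 0 | 0 to 10 | 10 | 5 | 10 |
| 20 | 20 to 30 | 10 | 25 | 30 |
| 40 | 40 to 50 | 10 | 45 | 50 |
| 60 | 60 to 70 | 10 | 65 | 70 |

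Any set of cut-offs on ROM puts all four in one stratum. Mean and peak angle separate them.

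**Step 3: a uniform correction.** A trunk at 45 to 55 degrees has ROM 55 − 45 = 10. Lower the angle by 20 degrees throughout, to 25 to 35, and ROM is 35 − 25 = 10. The measured change is 0 while the posture has shifted by 20 degrees.

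**Step 4: reversed order.** A posture held at 60 to 65 degrees has ROM 5, mean 62.5 and peak 65. A movement from 0 to 30 degrees has ROM 30, mean 15 and peak 30. Going from the first to the second lowers the mean by 62.5 − 15 = 47.5 degrees and the peak by 65 − 30 = 35 degrees, yet raises ROM by 30 − 5 = 25 degrees. If larger values count as higher risk, the held posture falls in the same or a lower stratum.

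**Step 5: where the problem vanishes.** If a sample includes the neutral position and the joint moves to one side of it only, the minimum is 0 and ROM = max − 0 = peak angle. Excursion and peak angle then agree. The misgrading arises in samples that stay away from neutral.

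**The case against.** The strongest reply is that no sentence says outright that the strata use the maximum-minus-minimum value. The definition stands in Motion Analysis, which does not mention RULA. The stratified outcome is named elsewhere. Table 1 gives RULA its own row, and the Ergonomic Risk section treats it as an established instrument with its own 1 to 7 score. The authors may be using range of motion loosely for whatever joint position RULA grades, and may intend to score actual angles. A journal article may also leave processing steps to a fuller document.

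Much of this stands. A reader might infer that the plan certainly computes the strata from the excursion, or that every non-neutral posture will be put in the wrong stratum. The article supports neither. The first is the literal reading, not an express statement. The second fails whenever a sample passes through neutral, as Step 5 shows. Nor are the primary outcomes touched: EMG fatigue and the Nordic questionnaire do not use range of motion.

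The reply does not remove the point. The outcome list, the RULA description and the Abbreviations all tie the strata to range of motion, and only one definition of that term is given. No section says how angles enter the RULA score. The point is therefore not missing detail: a stated formula does not suit a stated outcome.

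**Conclusion.** The concern holds as a conditional one. Taken literally, the plan grades an excursion against RULA limits. The strata can then place a sustained non-neutral posture level with or below a neutral one, and can miss a uniform correction. The invariance is exact and needs no knowledge of the RULA limits.

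The practical size is unknown. It depends on how often the sampled screw-tightening cycles stay away from neutral, and the article gives no angles from which to judge that. The conclusion rests on two assumptions: that range of motion means the same thing throughout the article, and that the strata are meant to reflect posture, as the mention of postural load implies.

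This should be fixed but does not threaten the study as a whole. The outcome is secondary, though it is the closest of those listed to the malposture aim. The recordings can be rescored, so nothing is lost if the wording is settled before analysis.

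**What to change.** In Data Collection and Outcomes, Motion Analysis and Ergonomic Risk, state that the RULA limits are applied to the joint angle relative to a defined neutral position. Prespecify one summary per cycle, for example the percentage of cycle time in each RULA category, or the peak angle. One is enough. Keep maximum minus minimum as a separate movement-excursion outcome. Say how the strata relate to the 1 to 7 RULA score, and correct the expansion of RULA in the Abbreviations.

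The cost is small: changes of wording and a little extra scripting. Marker trajectories are already recorded at 100 Hz, and the joint angles must be computed anyway to find their maximum and minimum. The one added requirement is a neutral reference for each joint, which an excursion does not need. Fix the summary before the data are examined, so that the angle measure is not chosen in the light of the results.

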### Questionnaires

#### Overview

For all the questionnaires, the Portuguese-validated version will be used.

#### Musculoskeletal Symptoms

To assess MSDs and symptoms associated with the working population, the Nordic Musculoskeletal Questionnaire will be used [21]. This questionnaire encompasses 27 questions (3 questions related to the 9 anatomical regions: neck, shoulders, wrists/hands, upper back, low back, hips/thighs, knees, and ankles/feet) with a binary response (yes or no) and a question to rate pain on a numerical scale [21]. This questionnaire presents a good test-retest reliability and good internal consistency [21]. To assess musculoskeletal symptoms before and after the shift on evaluation days, only the first question will be used and adapted for the recall period; instead of the last 12 months, a period of the last 8 hours will be considered.

#### Perceived Exertion

The Borg RPE scale is a tool for measuring an individual’s effort and exertion, breathlessness, and fatigue during physical work and so is highly relevant for occupational health and safety practice. In this scale, 6 corresponds to “No Effort” and 20 corresponds to “Extremely Hard” [27].

#### Ergonomic Risk

The RULA was selected to assess ergonomic risk in this study. This tool was developed to assess workers’ exposure to ergonomic risk work associated with musculoskeletal injuries of the upper limbs, taking into consideration biomechanical and postural load requirements of work task demands on the neck, trunk, and upper limbs. This instrument provides a simple scoring method based on the range of motion, which can identify joints at risk. The output of the RULA assessment tool is the final RULA score, which is a single score that represents the level of MSD risk for the job task being evaluated, ranging from a minimum of 1 to a maximum of 7 points [22].

#### Physical Activity Level

The level of physical activity will be assessed with the Rapid Assessment of Physical Activity questionnaire (RAPA). This version presents good internal and construct validity [28]. The RAPA evaluates the level and intensity of leisure-time physical activity, as well as strength and flexibility training in a 9-item, self-administered questionnaire [28].

#### Quality of Life

Participants' quality of life will be assessed with the Portuguese version of the EUROHIS-QOL 8-item index questionnaire [29]. This questionnaire presents a good internal consistency, test-retest reliability as well as construct, discriminant, and convergent validity [29]. In this quality-of-life measure, each of the domains (physical, psychological, social relationships, and environment) is represented by 2 items. The result is a global index, calculated from the sum of the 8 items, with a higher value corresponding to a better perception of quality of life [30].

#### Depression and Anxiety Symptoms

The Patient Health Questionnaire-9 (PHQ-9) will be used to assess signs of depression [31]. This tool reports to the last 2 weeks and consists of a depression module with 9 items, using a 4-point response scale, ranging from “0” (not at all) to “3” (nearly every day). The PHQ-9 presents good internal consistency, convergent validity, and criterion validity. Total scores of 5, 10, 15, and 20 represent cut points for mild, moderate, moderately severe, and severe depression, respectively [32]. Anxiety-related signs and their severity will be assessed by the General Anxiety Disorder 7-item scale (GAD-7) [33]. The GAD-7 index is obtained by adding the scores from the questionnaire, after having assigned 0 to 3, depending on the severity. The cutoff points 5, 10, and 15 classify the anxiety as none/normal (0-4), mild (5-9), moderate (10-14), and severe (15-21). In general, anyone who scores 8 or above can be considered as having significant anxiety symptoms [34]. This scale presents cultural adaptation, excellent internal consistency, internal validity, and very good reliability [33].

#### Sleep Quality

The Basic Scale on Insomnia Complaints and Quality of Sleep (ie, BaSIQS) questionnaire is based on a set of 7 questions assessing nocturnal experiences in terms of subjective sleep quality and symptoms of insomnia [35]. Except for the final 2 items, which are scored on a reversed 5-point Likert scale, all items are scored on a scale of 0 to 5, with higher scores indicating poorer sleep. The results on reliability, validity, and accuracy support the use of this questionnaire for research and practical purposes [35].

#### Subjective Fatigue

Fatigue will be assessed with the Functional Assessment of Chronic Illness Therapy- Fatigue. This 13-item tool measures an individual’s level of fatigue during their usual daily activities over the past week. Scoring is based on a 4-point Likert scale (4=not at all fatigued to 0=very much fatigued), with a ranging total score of 0 to 52 (0=worst possible score; 52=best possible score indicating no fatigue) [36]. This questionnaire presents high internal consistency, good convergent and divergent validity, and satisfactory test-retest reliability [37].

### Data Management and Monitoring

The collection and data storage will be made in digital format, including those from the questionnaires. The entered data will be checked for completeness, validity, and plausibility by a member of the research team.

### Data Analysis

Structured visual analysis techniques will be conducted to observe the effects of the intervention using a Single-Case Visual Analysis package for R. Graphical (RStudio) representations of data for each participant will be plotted considering primary and secondary outcomes on the y-axis and time on the x-axis. The results for each variable of interest will be compared in-between the different time points of the work shift and longitudinally considering each assessment day as a time point.

For each outcome (primary or secondary) and each moment mean, median, range, and stability envelope will be calculated. The level of change and difference between the first and last values of each period will be compared. The next step includes the calculation trend using the split middle method of trend estimation. After this procedure, percent of data points within the stability envelope (80% of data points between ±25% of median) will be considered. The final step is using the “freehand method” to evaluate data path [38].

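### The ±25%-of-median envelope and split-middle trend do not suit the yes/no symptom outcome, and for RPE and RULA the envelope depends on the scale's origin and level

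*Protocol article*

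**What the plan says.** The Data Analysis section of the Protocol article sets out one sequence: "For each outcome (primary or secondary) and each moment mean, median, range, and stability envelope will be calculated". The next step is the "calculation trend using the split middle method of trend estimation", after which the "percent of data points within the stability envelope (80% of data points between ±25% of median) will be considered". No outcome is exempted, and no alternative is given for binary or ordinal data. The same section also lists a plot for each participant, the difference between first and last values, and a freehand reading of the data path.

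Under Data Collection and Outcomes, "The primary outcomes are fatigue and musculoskeletal symptoms", the latter measured by the NMQ. The Musculoskeletal Symptoms section describes NMQ items "with a binary response (yes or no) and a question to rate pain on a numerical scale". For the measurements before and after the shift on evaluation days, however, "only the first question will be used and adapted for the recall period", which falls from 12 months to 8 hours.

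Among the secondary outcomes, the Borg RPE runs from 6 to 20 (Perceived Exertion). The RULA final score is described as "ranging from a minimum of 1 to a maximum of 7 points" (Ergonomic Risk), although the listed outcome is a stratification of range of motion by RULA limits. Each assessment covers five days (Study Procedure).

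**The concern.** A band defined as a percentage of the median presupposes a true zero and enough distinct values for the band to have a sensible width. A yes/no answer offers only two values. RPE starts at 6 and RULA at 1, so a percentage of the score reflects the choice of origin as well as the worker's variability.

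This matters because the stated analysis is visual, with no test, and each of the five workers is read individually. The envelope is also the only numerical stability criterion in the article, while Design and Setting relies on baseline stability returning before the second intervention phase. A label of stable or unstable that does not follow variability, or that moves against the symptoms, would mislead the reader of the plots.

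**Working it through.** The article gives no figure to reproduce here. The check applies its own rule to each scale.

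**Inputs.** Envelope = [0.75 × median, 1.25 × median]. A phase is read as stable if at least 80% of its points lie inside (Data Analysis). There are five days per assessment (Study Procedure). The adapted NMQ is asked before and after the shift, giving 5 points per region, or 10 if both are pooled. Assumption: answers are coded 0/1 per region, since the article does not say how regions are combined.

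**1. Envelope for a yes/no answer.**
- Median 0: [0, 0], which holds only 0.
- Median 1: [0.75, 1.25], which holds only 1.
- Median 0.5 (5 yes of 10): [0.375, 0.625], which holds no possible answer, so 0% are inside.

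With five days:

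| Symptomatic days | Median | Percent inside | Reading |
|---|---|---|---|
| 0 | 0 | 100 | stable |
| 1 | 0 | 80 | stable |
| 2 | 0 | 60 | unstable |
| 3 | 1 | 60 | unstable |
| 4 | 1 | 80 | stable |
| 5 | 1 | 100 | stable |

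The percentage is the share of the commoner answer. It is the same for 1/5 and 4/5. It rises when symptoms fall from 2/5 to 0/5 (60% to 100%) and drops when they fall from 5/5 to 3/5 (100% to 60%).

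**2. Median for a yes/no answer.** The possible decreases in symptomatic days number 6 × 5 / 2 = 15. The median stays put for the 3 pairs within {0, 1, 2} and the 3 within {3, 4, 5}: 6 of 15. It moves in the other 9.

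**3. Split-middle slope for a yes/no answer.** All possible series were enumerated.
- n = 5, middle point omitted: 32 series give five slopes: 0 (12 series), ±1/6 (8 each) and ±1/3 (2 each).
- n = 10: 1,024 series give three slopes: 0 (512) and ±0.2 (256 each). In 260 of the 1,024 (25%) the slope is 0 although the two halves differ in the number of yes answers.

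**4. Number of symptomatic regions, 0 to 9 (assumed summary).** Median 0 still gives [0, 0]. Medians 1, 2 and 3 admit only the median itself (for example, 3 gives [2.25, 3.75]). A count therefore does not rescue the envelope at low symptom levels.

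**5. RPE, 6 to 20.** Median 12 gives [9, 15], so 9 to 15 are accepted. Re-based to zero, the median is 12 − 6 = 6 and the envelope is [4.5, 7.5]. The accepted values are 5 to 7, which is RPE 11 to 13. On the scale as published, median 6 accepts 6 to 7 and median 16 accepts 12 to 20.

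**6. RULA, 1 to 7.** The series 4, 3, 5, 4, 4 has median 4 and envelope [3, 5]: 5/5 = 100% inside. One point better throughout, 3, 2, 4, 3, 3 has median 3 and envelope [2.25, 3.75]: 3/5 = 60% inside. The spread is identical, but the label changes from stable to unstable.

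**The case against.** A reader might go further and infer that the plan gives meaningless results for all three scales, that it cannot register a fall in symptoms, or that only the mean carries information on the NMQ. The documents do not support any of these.

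- In 9 of the 15 decreases the median does move, and in the other 6 the percentage inside changes. The fault is that this percentage ignores direction.
- The plan also lists the range, the first-to-last difference, individual plots and the data path. Every yes/no answer can be plotted, and the envelope is described as a stability check, not as the test of effect.
- Split-middle on 0/1 data is coarse but can still show direction.
- For RPE and RULA, medians and split-middle trends are legitimate on ordinal scores. Only the percentage band is at fault.

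A reader might also conclude that the numerical pain rating should be restored as the daily symptom outcome. That would replace an 8-hour symptom question with a different construct. The article gives no recall period for the rating, and the existing answers can be summarised adequately without it.

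The objection that the study is small and exploratory is fair. It lowers the weight of the point. It does not remove it, because the recipe is stated for every outcome and is not left to a later document.

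**Conclusion.** The point holds in a limited form. For the yes/no NMQ answers, a primary outcome, the envelope is degenerate, its percentage is blind to direction, 6 of 15 possible decreases over five days leave the median unchanged, and the split-middle slope is too coarse to be useful. For RPE and RULA-based scores only the envelope fails, because its width depends on the scale's origin and level.

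The NMQ figures assume 0/1 coding per region with 5 points (10 where stated). The RULA example uses the 1 to 7 final score. Risk strata are ordinal too, so the same objection applies, though the example's numbers would differ. The point does not touch EMG fatigue, the other primary outcome.

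Severity is should-fix: the raw data and plots survive, and the rule can be corrected without changing data collection.

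**What to change.** Amend the Data Analysis text as follows.

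- **NMQ:** summarise each phase as the proportion of symptomatic days (or shifts) per region and the number of symptomatic regions. Plot both without the envelope or split-middle line.
- **RPE and RULA-based scores:** keep the median and split-middle trend. Replace ±25% of the median with an absolute band in scale points, with its width chosen and justified before data are seen.
- **Ratio-scale outcomes (EMG, kinematics, cycle duration):** keep ±25% of the median.

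The cost is a change of text, with no new measurement, visit or staff. The downside is that stability criteria will differ by type of outcome, which the report should state.
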